### Recruitment Process

Two schools in NSW expressed interest in participating in the study during the 2025 school year. Upon being are recruited, a brief outlining the intervention design is emailed to principals, including the length of the intervention, its theoretical framework, and requirements for teachers and participating students. Meetings with participating schools will take place, and a co-design plan as well as professional development time will be organized. Consent forms and participation information statements will be distributed to the schools for collection from principals, teachers, students, and parents or guardians.

### Eligibility Criteria

Explicit eligibility criteria must be met for participation in the study. Students may participate if they (1) are enrolled in year 5, 6, or 8 at a participating independent or government secondary school in NSW; (2) have completed the pretest questionnaire; and (3) have written consent from parents or guardians.

### Intervention Design

This intervention will focus on providing opportunities for students to develop social skills in PE classes. Teachers will act as facilitators, and researchers will codevelop and adapt the intervention programs with them using a co-design process. A teacher professional development program will be administered before intervention commencement to ensure that teachers are familiar with the TPSR framework. Students will take part in focus groups before and after the intervention and will complete surveys measuring social outcomes. The researchers will be available for communication with teachers to maintain intervention integrity and to ensure that issues are addressed efficiently. Teachers will run their PE lessons with the TPSR framework embedded within their existing programs, minimizing additional workload. Examples of TPSR strategies that may be featured within lessons are provided in Table 1.

Before intervention commencement, students and teachers from the participating schools will complete preintervention testing, which will include surveys. Students at each school will then take part in the 10-week intervention and complete a postintervention test similar to the preintervention test. Focus groups will also be conducted during the posttest period. There will be a follow-up 5 weeks after the intervention. In line with the mandated requirements of the schools, students will participate in 1 PE lesson per week, which is standard practice in NSW schools. The duration of each lesson will depend on the school, with 45 to 60 minutes being typical in NSW schools. Social outcomes (personal responsibility and social responsibility) will be the primary focus of the intervention, as per the measurement tool.

### Data Analysis

This study will use a nonrandomized controlled trial design with a qualitative evaluation of feasibility and acceptability, integrating both qualitative and quantitative data to evaluate the impact of the TPSR intervention.

#### Quantitative Analysis

Quantitative data from the PSRQ, PACES-PE, and TPSR will be analyzed using SPSS software (version 30.0; IBM Corp). Internal consistency of the scales will be assessed using Cronbach α. The PSRQ will assess students’ self-perceived levels of personal and social responsibility, and the PACES-PE will assess enjoyment in PE. ANOVA will be conducted to compare mean scores before and after the intervention for both questionnaires. TARE data will be collected through lesson observations by the research team 3 times during the 10-week intervention period, and interrater reliability will be assessed using Cohen κ. Frequencies and mean scores of the TPSR strategies will be examined descriptively and across time to explore implementation fidelity. A repeated measures multivariate ANOVA will be performed to provide a more complex analysis of the findings and a more comprehensive view of how the intervention affects multiple variables simultaneously.

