### Study Design

The protocol was developed according to the SPIRIT (Standard Protocol Items: Recommended for Interventional Trials) statement (Multimedia Appendix 1).

The study will use a nonrandomized controlled trial design with a qualitative evaluation to assess feasibility and acceptability. This method has been chosen for several reasons. First, one of the criticisms against the TPSR model is that it favors qualitative studies and has been underresearched using quantitative methodologies [11]. To address this, we will use both qualitative and quantitative methods in this study. The concern regarding the limited use of quantitative approaches was echoed in a systematic review on TPSR interventions that found that only 4 of the 22 included studies used exclusively quantitative methods, questioning the validity of the framework outside of qualitative research [26]. Studies have consistently called for greater use of quantitative analysis of the TPSR framework in research [10,11,26]. Furthermore, to obtain the most accurate representation of the effect of the framework in Australian schools, teachers, and students, this approach is deemed most suitable because it uses both qualitative and quantitative analysis and is able to factor in a complex landscape such as education [27]. In this study, data will be collected through student surveys, focus groups, teacher reflection journals, and the Tool for Assessing Responsibility-Based Education (TARE).

We will recruit at least 6 classes from each school participating in the intervention, which will amount to approximately 3 classes in the control group and 3 in the experimental group (Figure 1).

Upon recruitment of the schools and selection of individual classes by each principal, researchers will collaborate with intervention facilitators to implement the TPSR framework during the intervention “season.” Table 1 presents example strategies that can be implemented in a TPSR study and will be shared with teachers during the co-design process.

A timeline of the intervention is presented in Table 2.

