### Participants

The participants in this study will be students from years 5, 6, and 8. Each intervention group in the study will need to have 77 students and a matched control group of the same size to detect 2-tailed statistical significance (*P*<.05) with 80% power (1−β=0.8). Two schools in the western suburbs of Sydney have been recruited to participate in the study: one is a government high school, and the other is an independent K-12 school. They have been chosen through professional networks who expressed interest in the TPSR study. Students in NSW generally participate in 1 PE lesson per week, which is where the intervention will take place. PE lessons in NSW high schools are delivered to students from years 7 to 10 and focus on skills development, alongside one or two sport lessons focused on game play.

Consent will be obtained from parents, students, and the school principals in line with the ethics requirements of the University of Sydney. Participants’ personal information and school names will be deidentified in all publications arising from the study. Students and teachers will also be briefed on the intervention before study commencement and given the opportunity to ask questions. Participants will be allowed to withdraw from the intervention at any time. All data collected, including data from focus interviews, surveys, meeting minutes, and consent forms, will be stored securely and encrypted with a password. If parents request details of intervention results, a lay summary will be provided.

Fidelity and acceptability will be addressed through teacher expertise and training, intervention location, timetabling, and time spent on the intervention. Teachers will participate in a professional development program before starting the intervention. The purpose of this program is to familiarize teachers with the TPSR framework and to facilitate the co-design of strategies and activities to integrate the framework into programs. This approach also means that students do not have to build relationships with or adapt to outside facilitators. Furthermore, it does not incur additional funding for the school or research team. The professional development program will comprise a 3-hour, face-to-face learning block before the intervention and ongoing check-ins with teachers using Zoom (Zoom Video Communications, Inc) for the duration of the intervention.

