### Measurement Tools

The Personal and Social Responsibility Questionnaire (PSRQ) will be used to measure the primary outcomes of the study: personal responsibility, social responsibility, and leadership. This questionnaire has been used in previous TPSR studies and has been deemed valid and reliable [30,31]. It consists of 14 items split into 2 categories (personal responsibility and social responsibility) [30]. Participants will complete the PSRQ in the pretest and posttest phases of the intervention and will be assured that there are no right or wrong responses and that their responses will remain anonymous. The TARE is an observational tool aligned with the TPSR model. The second part focuses on whether teachers have included elements such as modelling respect and setting expectations within their lessons [32]. The secondary outcomes of the study will be enjoyment, feasibility, and acceptability. These outcomes will be measured using the Physical Activity Enjoyment Scale–Physical Education version (PACES-PE), which is an 11-item measurement tool designed to measure enjoyment levels in adolescent children using a Likert scale and revised, student-friendly questions [33]. The PACES-PE has been used in PE-based studies previously and demonstrated positive results in female adolescent populations, particularly through the link between enjoyment and increased rates of physical activity [33].

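### The per-questionnaire before/after ANOVA names no within-student term or baseline covariate; run unpaired, it ignores the pre/post pairing and its error rate is not controlled

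*Protocol article*

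**What the plan says.** The Quantitative Analysis section of the protocol article gives one test for the two student questionnaires: "ANOVA will be conducted to compare mean scores before and after the intervention for both questionnaires". It does not say whether this ANOVA is independent-groups, repeated measures or mixed. It names no factor other than before/after and no covariate. Later in the same paragraph it adds that "A repeated measures multivariate ANOVA will be performed to provide a more complex analysis of the findings".

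The data are paired by design. Under Measurement Tools, "Participants will complete the PSRQ in the pretest and posttest phases of the intervention". Under Eligibility Criteria, students may take part only if they "have completed the pretest questionnaire". Table 2 places the PSRQ and PACES-PE in term 2 week 8 and again in term 3 week 10. Measurement Tools also assures students that "their responses will remain anonymous", and the article describes no linkage code.

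**The concern.** Two scores from one student are usually positively correlated. An ANOVA that treats them as scores from two different students leaves the stable differences between students in the error term. The estimated change is unaffected, but its standard error is wrong.

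The wording invites this reading. The authors use the repeated measures label for the multivariate analysis, which they present as the more complex one, and leave it off the per-questionnaire test. The PSRQ is the student questionnaire for the primary outcomes, so its results would carry wrong P values and confidence intervals. The ANOVA and the repeated measures MANOVA could also disagree on the same data merely because one uses the pairing and the other does not.

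**Working it through.** **Inputs from the article.** Participants: "Each intervention group in the study will need to have 77 students and a matched control group of the same size", for "2-tailed statistical significance" at P<.05 with 80% power. Study Design: at least 6 classes per school, "which will amount to approximately 3 classes in the control group and 3 in the experimental group". Abstract: about 90 students per school, so 90/6 = 15 per class.

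**Inputs not in the article (assumptions).** Pre/post correlation ρ of 0.3, 0.5 or 0.7; a change of 0.3 SD; an intraclass correlation (ICC) of the change score from 0 to 0.20.

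**The plan's own figure.** No effect size is given, so 77 can only be back-solved. For two groups, d = √2 × (1.960 + 0.842)/√77 = 0.45 (0.454 with the t distribution). Entering d = 0.45 returns 78 per group. This is consistent with 77 but does not reproduce it. Below, 77 serves only as the number of students measured twice.

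**Step 1: unpaired test on paired data, no class effect** (scores in SD units).
- Standard error used: √(2/77) = 0.161.
- True standard error: √(2(1−ρ)/77), which is 0.114 at ρ = 0.5.
- Ratio: 1/√(1−ρ).
- True error rate: 2 × [1 − Φ(1.96/√(1−ρ))].
- Power for 0.3 SD at ρ = 0.5, unpaired: the cut-off is 1.96 × 0.161 = 0.316, so 1 − Φ((0.316 − 0.3)/0.114) = 44%.
- Same, paired: 1 − Φ(1.96 − 0.3/0.114) = 75%.

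| ρ | SE ratio | True error rate | Power, unpaired | Power, paired |
|---|---|---|---|---|
| 0.3 | 1.20 | 1.9% | 45% | 60% |
| 0.5 | 1.41 | 0.56% | 44% | 75% |
| 0.7 | 1.83 | 0.03% | 43% | 92% |

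A simulation of 20,000 runs per correlation gave unpaired error rates of 1.8%, 0.5% and 0.06%, and paired rates of 5.0% to 5.1%.

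**Step 2: add class clustering of the change.** With m students per class, the true variance is multiplied by DEFF = 1 + (m−1) × ICC. The unpaired test's error rate becomes 2 × [1 − Φ(1.96/√((1−ρ) × DEFF))]. At m = 15 and ρ = 0.5:

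| ICC of change | DEFF | Error rate, unpaired test | Error rate, paired test without a class term |
|---|---|---|---|
| 0 | 1.0 | 0.6% | 5% |
| 0.05 | 1.7 | 3.4% | 13% |
| 0.10 | 2.4 | 7.4% | 21% |
| 0.20 | 3.8 | 15.5% | 31% |

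The unpaired test passes 5% when (1−ρ) × DEFF = 1, that is, at ICC = ρ/((1−ρ)(m−1)). This is 0.071 at ρ = 0.5, 0.031 at ρ = 0.3 and 0.167 at ρ = 0.7.

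**The case against.** The article says only ANOVA, a family that includes the repeated measures form, and a before/after comparison is naturally within-student. A condensed article may leave the type to a fuller plan. The repeated measures MANOVA cannot be run without linked records, and a completed pretest is an entry condition. Both suggest that the team may intend a paired analysis. A reader might infer that the plan definitely uses an unpaired test, or ignores pairing altogether. The text supports neither.

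A reader might also infer that standard errors are certainly too large and the error rate certainly below 5%. That requires an unpaired run, a positive correlation and little class clustering. Step 2 shows that the direction reverses at a modest ICC. It also shows that moving to a paired test without a class term could raise false positives rather than cure the problem.

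These objections limit the certainty and the direction of the claim. They do not remove the point. The sentence does fix a test for the questionnaires, separates it from the analysis labelled repeated measures, and leaves out the term that a before/after comparison of the same students needs. Two errors that partly offset each other do not make a valid 5% test. The MANOVA is a joint test of several variables, and the article does not say that it replaces the per-questionnaire result.

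**Conclusion.** The point holds conditionally. As worded, the per-questionnaire ANOVA has no within-student term and no baseline covariate. If it is run on independent groups, then without class clustering the standard error is about 1.2 to 1.8 times too large, the error rate is about 1.9% to 0.03%, and power for a 0.3 SD change falls from about 75% to 44% at correlation 0.5. The correlations, the 0.3 SD change and the ICCs are assumptions, because the article gives none of them. With 15 students per class and correlation 0.5, clustering of the change above an ICC of about 0.07 takes the error rate past 5%. The supportable conclusion is therefore an uncontrolled error rate, not a certainly conservative one. The wording should be changed, and the better analysis uses data that are already planned.

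**What to change.** Replace the ANOVA sentence with one model for each PSRQ subscale and for the PACES-PE that uses the student's own pretest. There are two suitable forms:

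- A repeated measures or mixed model with time within student, arm between students, and arm-by-time as the tested effect.
- An ANCOVA of the posttest on arm, adjusted for the pretest.

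Both need a class term. In the repeated measures form it must let classes differ in their change, because a class intercept alone cancels from the change. Either form also supplies the intervention-versus-control contrast that the present sentence does not name. The article should say how these results relate to the repeated measures MANOVA.

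State that pretest and posttest are linked by a study code, and reconcile this with the assurance of anonymity. The MANOVA needs the same linkage.

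Cost: the change to the analysis text is small and needs no new measurements. Students missing a wave drop out unless a mixed model is used. The class term will widen the intervals, since there are only about 3 classes per arm in each school. The Results section says that data collection has begun, so linkage depends on a code having been collected at pretest. If none was, neither the proposed models nor the planned MANOVA can be run, and the article should say so.

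### The only contrast stated for the questionnaires is before versus after the intervention; the comparison with the control group is not named

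*Protocol article*

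**What the plan says.** The design is controlled throughout the protocol article. Study Design plans, within each school, "approximately 3 classes in the control group and 3 in the experimental group". Participants sizes the trial for two groups: "Each intervention group in the study will need to have 77 students and a matched control group of the same size". The opening of Data Analysis repeats the design: "This study will use a nonrandomized controlled trial design with a qualitative evaluation of feasibility and acceptability".

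Quantitative Analysis then gives the comparison for the PSRQ and PACES-PE: "ANOVA will be conducted to compare mean scores before and after the intervention for both questionnaires". It adds a second analysis: "A repeated measures multivariate ANOVA will be performed to provide a more complex analysis of the findings". The stated purpose of that second analysis is to look at several variables together. Nothing in Data Analysis names an arm factor, a group-by-time term or a between-arm difference.

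**The concern.** The article does not leave the questionnaire contrast to a later document. It states one, and the contrast is time. That conflicts with a trial that recruits and sizes a concurrent control group.

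A before-after change adds any TPSR effect to whatever else moves scores between the two surveys. Table 2 puts the pretest in Term 2 week 8 and the posttest in Term 3 week 10, so students are older, in a new term, and answering the same self-report items a second time. The drift could also be downward: the Background says that engagement in PE falls with age, and a fall common to both arms would hide a real benefit. Without randomization, the concurrent control classes are the design's main means of separating TPSR from such shared change. If they are not in the contrast, the stated aim of showing the impact of TPSR is not met.

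**Working it through.** **The plan's own figure.** Participants gives 77 students per group for 80% power at two-sided 0.05, with no effect size, SD or pre-post correlation. The 77 therefore cannot be reproduced, only inverted. For two independent means, d = (1.960 + 0.842) × sqrt(2/77) = 2.802 × 0.161 = 0.45 SD.

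**Inputs for the check.**
- From the protocol article: n = 77 in the intervention group, an equal control group, two-sided 0.05.
- Assumed, because the article gives neither: pre-post correlation r of 0.6 (range 0.5 to 0.7), and a drift common to both arms of 0.1, 0.2 or 0.3 SD.
- True TPSR effect set to zero; clustering by class ignored.

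**Before-after test in the intervention group.** The standard error of the mean change, in SD units, is sqrt(2(1 − r)/n) = sqrt(0.8/77) = 0.102. The chance of a significant result is approximately P(Z > 1.96 − drift/SE), plus a negligible opposite tail.
- Drift 0.1: drift/SE = 0.98, about 17%.
- Drift 0.2: drift/SE = 1.96, about 50%.
- Drift 0.3: drift/SE = 2.94, about 84%.

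At a drift of 0.2 SD the result depends on r:
- r = 0.5: SE = sqrt(1.0/77) = 0.114, about 42%.
- r = 0.7: SE = sqrt(0.6/77) = 0.088, about 62%.

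Exact noncentral t calculations agree: 16%, 49% and 83% for the three drifts at r = 0.6, and 41% to 61% at a drift of 0.2 SD across r = 0.5 to 0.7. If the before-after test pooled both arms (n = 154), the 0.2 SD drift would give 69% to 89%.

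**Between-arm test of change.** A shared drift cancels in the difference between the arms' mean changes. In 20,000 simulated trials with r = 0.6 and 77 per arm:
- No drift: the before-after test rejected in 4.7% and the between-arm test in 5.1%.
- Drift 0.2 SD: the before-after test rejected in 49.5% and the between-arm test in 4.9%.

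**Does the correction cost power?** With 77 per arm and a true difference in change of 0.45 SD, power = Φ(2.802/sqrt(2(1 − r)) − 1.96). This is 80%, 88% and 95% for r = 0.5, 0.6 and 0.7, again ignoring clustering. On that basis the planned sample suits the between-arm contrast; clustering by class would lower these figures.

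**The case against.** The strongest reply is that a group factor is implied. Data Analysis opens by restating the controlled design, and an ANOVA or repeated measures MANOVA with group as a factor is compatible with every sentence. This is also a condensed article, and lists of model terms are often left to a fuller plan. Part of this stands. A reader might infer that the controls will be excluded from the analysis, but the text does not show that: it nowhere limits the ANOVA to intervention students. What does not stand is that this is mere missing detail. The sentence says what is compared, and that comparison is not the one the design calls for.

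Other stronger readings also go too far:
- A reader might call the before-after ANOVA the main analysis. The article labels no analysis main or primary.
- A reader might say that the MANOVA could give no between-arm result for the PSRQ. With group included, it would yield group-by-time tests for each measure as well as the omnibus test. The defect is only that group is not named.
- A reader might add regression to the mean. Eligibility sets no score threshold and principals select the classes, so the documents give it little support.
- A reader might conclude that baseline-adjusted analysis is the only valid remedy. In a nonrandomized comparison of intact classes, adjustment for pretest and difference in change can disagree when baselines differ, and neither is automatically right.

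**Conclusion.** The point holds for the text as published: the stated contrast is the wrong one for a controlled trial, and no other sentence in Data Analysis repairs it. Followed literally, a modest shared drift of 0.2 SD would produce a significant result in about half of trials with no TPSR effect (42% to 62% for correlations of 0.5 to 0.7). These rates rest on assumed drift and correlation, on the literal before-after reading, and on no clustering. The direction of the problem does not depend on those values.

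The between-arm contrast removes only change that both arms share. Because classes are not randomized, differences between arms in how scores would have moved anyway remain possible, and the interpretation should say so.

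**What to change.** In Quantitative Analysis, replace the before-after sentence with a between-arm comparison as the primary analysis of each PSRQ subscale, and use the same analysis for PACES-PE. Two forms are acceptable: the group-by-time difference in change, or the posttest difference adjusted for the same student's pretest score. Prespecify one, keep the other as a sensitivity analysis, and allow for class and school in both. Name group as the between-subjects factor in the repeated measures MANOVA and treat it as supportive. Report within-arm changes descriptively only.

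Intervention Design describes the posttest in these words: "Students at each school will then take part in the 10-week intervention and complete a postintervention test similar to the preintervention test". The revision should state explicitly that control students complete both surveys as well.

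The cost is wording plus linking each student's pretest and posttest. The repeated measures analysis already requires that link, but Measurement Tools promises anonymous responses and describes no linkage, so a coded identifier should be stated. Both groups and both time points are already part of the design, and completing the pretest is an eligibility criterion. The Results section says that collection began in August 2025 with analysis scheduled for October 2025, so the wording should be settled before outcome data are examined.

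### Whole classes are assigned (about 6 TPSR and 6 control), but the named ANOVA and MANOVA have no class term, so the 5% level is exceeded if classmates' scores are correlated

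*Protocol article*

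**What the plan says.** **Assignment.** Study Design starts the implementation step with "Upon recruitment of the schools and selection of individual classes by each principal". On numbers it says "We will recruit at least 6 classes from each school participating in the intervention". It expects these to divide evenly, about 3 per arm in each school. Participants gives two schools, so there are about 12 classes (a minimum), of which about 6 receive TPSR.

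**Delivery.** Intervention Design: "Teachers will run their PE lessons with the TPSR framework embedded within their existing programs". The abstract likewise has the students' usual PE teachers deliver the programme in timetabled lessons.

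**Analysis.** Quantitative Analysis names ANOVA of PSRQ and PACES-PE mean scores before and after the intervention. It then adds "A repeated measures multivariate ANOVA will be performed to provide a more complex analysis of the findings". Neither method is given a term for class, teacher or school.

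**Sample size.** Participants: "Each intervention group in the study will need to have 77 students and a matched control group of the same size". The basis is a two-sided 5% test "with 80% power (1−β=0.8"). The count is in students. No effect size, ICC or design effect is given, and clustering is not mentioned anywhere in the article.

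**The concern.** Students in one class share a teacher, a set of lessons and a peer group. The lesson content is co-designed with the teachers and can be changed during the term in response to their journals, so the teacher is part of the treatment. The primary outcomes are personal responsibility, social responsibility and leadership, which the programme tries to develop through group activity. Some correlation between classmates is therefore to be expected.

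ANOVA and repeated measures MANOVA without a class term treat students as independent. The repeated measures part deals with correlation within one student over time, not between classmates. If the between-classmate correlation is above zero, the standard error of the arm effect is too small. One or two unusual teachers could then produce a significant result. This affects the primary outcomes of a trial that presents its quantitative component as an answer to criticism of earlier TPSR research.

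**Working it through.** **1. Inputs.** From the article: two-sided alpha 0.05, power 80%, 77 students per group (Participants); at least 6 classes per school, about 3 per arm (Study Design); 2 schools (Participants); about 90 students per school (abstract). Assumed: ICC 0.02, 0.05 and 0.10, because the article gives none.

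**2. The plan's own figure.** No effect size or SD is stated, so 77 can only be solved backwards. For an unclustered two-group comparison, d = (1.96 + 0.84) × √(2/77) ≈ 0.45 (0.452 by normal approximation, 0.454 by t). In the forward direction, d = 0.45 gives 78 (normal) or 79 (t) per group. The figure is thus consistent with a calculation that treats students as independent.

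**3. Class size.** 77/6 ≈ 12.8 per class. If 90 per school covers all 6 classes, 90/6 = 15. Only if the 90 covers the 3 TPSR classes alone is it 90/3 = 30.

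**4. Type I error of a student-level test.** Design effect DE = 1 + (m − 1) × ICC. True two-sided error = 2 × [1 − Φ(1.96/√DE)]. Example with m = 12.8 and ICC 0.05: DE = 1.59, √DE = 1.26, error = 12.0%. The simulation used 6 v 6 classes, no true effect and a two-sample t test (20,000 runs per cell; 10,000 for m = 30).

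| Students per class | ICC | DE | Error, formula | Error, simulated |
|---|---|---|---|---|
| 12.8 (13 in simulation) | 0.02 | 1.24 | 7.8% | 8.1% |
| | 0.05 | 1.59 | 12.0% | 12.4% |
| | 0.10 | 2.18 | 18.5% | 19.0% |
| 15 | 0.02 | 1.28 | 8.3% | 8.2% |
| | 0.05 | 1.70 | 13.3% | 14.0% |
| | 0.10 | 2.40 | 20.6% | 20.6% |
| 30 | 0.05 | 2.45 | 21.1% | 21.2% |

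At ICC 0 the simulated student-level error is about 5%. A t test on class means stays between 4.8% and 5.4% in every cell run.

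**5. Power once class is respected.** 77 per arm in 6 classes, d = 0.45, SE = √(2 × DE/77), t test on 10 degrees of freedom (12 classes minus 2 arm means).

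| ICC | Effective n per arm (77/DE) | Power |
|---|---|---|
| 0.02 | 62 | 62% |
| 0.05 | 48 | 52% |
| 0.10 | 35 | 40% |

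**6. Degrees of freedom for a mixed model.** 12 classes minus intercept, arm and school leaves about 9. Adding year level (5, 6, 8) costs two more and leaves about 7.

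**7. School and year level.** Participants says that high school PE covers years 7 to 10, so of the three study years the government high school can supply only year 8. If the K-12 school supplies only years 5 and 6, year level determines school completely and a model with both terms cannot be fitted. Otherwise the two remain strongly entangled.

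**The case against.** **A condensed article may leave model terms to a fuller plan, and it never says student-level.** True: that reading is inferred. But the article does name its methods, those methods carry no class term, and the sample size is counted in students and matches an unclustered calculation. This is a method already fixed, not a detail deferred.

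**The inflation is conditional.** This stands. A reader might infer that the 5% level certainly fails, but without an ICC in the article that cannot be said.

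**The percentages are for a two-group comparison of one score, not for the planned pre/post tests.** This also stands. For a group-by-time effect the relevant ICC is that of the change scores, because stable class differences cancel. As an illustration, assume a posttest ICC of 0.10, class effects correlated 0.8 over time and student residuals 0.6. The change-score ICC is then (2 × 0.10 × 0.2) / (2 × 0.10 × 0.2 + 2 × 0.90 × 0.4) = 0.04/0.76 ≈ 0.05. With 15 per class the error is then about 14%, not 21%. Other correlations could leave the ICC unchanged or raise it.

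**The worst figures need large classes.** Thirty per class requires reading the 90 students per school as TPSR classes only, which the abstract does not say. The 13 to 15 range is the safer basis.

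**Missing data.** A reader might add that repeated measures MANOVA drops students with a missing measurement. That is a separate matter: a completed pretest is an eligibility condition, and a posttest-on-pretest model also loses students without a posttest.

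**Conclusion.** The point holds in conditional form. Assignment and delivery are by class, with about 12 classes in the trial. It would be wrong to infer that TPSR reaches all 12; it reaches about 6. The named analysis and the sample size make no allowance for this. With 13 to 15 students per class, a nominal 5% student-level comparison has a true error of about 8% at ICC 0.02, 12–14% at 0.05 and 19–21% at 0.10. Larger classes would make it worse.

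These figures rest on an assumed ICC (that of the change scores for a group-by-time test), on 6 classes of equal size per arm, and on each class being a separate unit. If one teacher takes several classes there are fewer independent units.

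Nor should a reader infer that a class-level model makes the treatment estimate valid. It corrects the standard error; selection bias from classes chosen by principals without randomization is untouched.

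**What to change.** In Quantitative Analysis, before the data are analysed:

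- Make the primary analysis a linear mixed model of posttest PSRQ on arm, pretest PSRQ and school (fixed), with a random intercept for class, or for teacher where one teacher takes several classes. Use REML with Kenward-Roger or Satterthwaite degrees of freedom (about 9 with 12 classes).
- Do not add year level alongside school unless the class list shows that the two can be separated. If a combined school-by-year stratum is used instead, state the reduced degrees of freedom.
- Add a comparison of class means as a sensitivity analysis.
- Record a class and teacher code with each deidentified survey.
- In Participants, restate the power with an assumed ICC.

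**Cost.** No extra students or visits, but more than a change of wording. Measurement Tools assures students that responses stay anonymous, so class and teacher codes must fit that assurance; linking pretest to posttest already needs some code. Intervals will be wider, and the stated 80% power no longer holds with 77 per group. The Results section says that recruitment ended in December 2024 and data collection began in August 2025, so adding classes is not a simple remedy. The lower power should be reported as such.
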